**2. AIM**

1. To compare the effectiveness of a lifestyle intervention in early pregnancy with the usual antenatal care in reducing the prevalence of GDM (primary outcome) and the proportion of infant born large for gestational age (LGA) and macrosomia (secondary outcomes) in high risk Chinese pregnant women in Hong Kong
2. To explore the effectiveness of a lifestyle intervention in early pregnancy as compared to the usual antenatal care in improving other obstetric maternal outcomes and fetal and neonatal outcomes (tertiary outcomes) in high risk Chinese pregnant women in Hong Kong

**3. PLAN OF INVESTIGATION**

| **Study design**   | This will be a parallel group, single-blind randomized controlled trial. The study will last for 24 months and will be divided into 5 phases including study preparation (1st to 3rd month), subject recruitment (4th to 9th month), data collection (4th to 21st month), data entry (4th to 22nd month), data analysis and report writing (19th to 24th month). The study will be conducted in accordance with the Declaration of Helsinki. | | --- | |  |   **Subjects**  **Subject recruitment** - Subjects with gestational age <=12 weeks will be recruited using a convenience sampling method at the first antenatal (AN) booking visit of the Prince of Wales Hospital (PWH). Subjects will be eligible for the study if they fulfil the following inclusion and exclusion criteria. The research staff will screen clients attending the AN clinic, check for eligible subjects, explain study details and invite them to join the study. Written consent will be obtained from all subjects.  **Inclusion criteria**   - Chinese origin - Reside normally in Hong Kong - Singleton pregnancy - Gestational age <= 12 weeks at the time of recruitment - Could speak and understand Chinese - Fulfill at least one of the following criteria for high risk of GDM at the time of recruitment based on the update hospital protocol implemented since 1st May 2014   - Maternal age >= 35 years old at expected date of confinement.   - Prior history of GDM or birth of child >= 4 kg   - Pre-pregnant BMI or BMI at 1st trimester >= 25 kg/m2   - Family history of diabetes at 1st degree relatives - Willing to give informed written consent and follow the study procedures   **Exclusion criteria**   - Concurrent participation in any clinical trial or study - With renal, liver or thyroid dysfunction, cognitive impairment, or any other indication of a major medical or psychological illness, as judged by the investigators as ineligible to participate the study - Multiple pregnancies - Pre-existing DM - With physical restriction that prevents from exercising - Substance abuse |
| --- | --- | --- |
|  |
| **Methods**  **Study outcomes –** The primary outcome will be the proportion of subjects developed GDM at 24-28 weeks gestation in in both groups as measured using a 75 g 2-h oral glucose tolerance test (OGTT). The secondary outcomes will include the proportion of neonates born with LGA (>=95th percentile of the customized birth weight) and macrosomia (>=4 kg at birth) in both groups. The secondary outcomes are chosen since infants born with larger size, in particular those born with GDM mothers were associated with higher future metabolic risk as compared to those born appropriate-for-gestational age with non-GDM or GDM mothers (19).  **Sample size calculation** – Sample size was calculated based on the primary outcome, i.e. the proportion of subjects developed GDM at 24-28 weeks of gestation between the two study groups. A previous lifestyle intervention trial in obese pregnant women showed that 6% subjects developed GDM in the intervention group compared to 29% in control group (p<0.05) (20). Based on these figures, the sample size estimates for a two-sided test will be 42 per group with power of 80% at a 5% significance level to detect an 83% reduction in the odds of decreased GDM in the intervention group when compared to the control group (20). However, a more conservative sample size estimate is used as the proposed lifestyle modification program (LMP) has been modified with less frequent dietetic sessions compared with that used in our previous publications. Therefore, a sample size of 73 per group with power of 90% at a 1% significance and two-sided test will be used. Assuming 30% lost to follow-up rate and 5% miscarriage rate, a final sample size of 110 subjects per group will be required.  **Trial procedures** – Eligible subjects will be randomized in 1:1 ratio to participate in the LMP or receive usual care from the time of recruitment (i.e. <= 12 weeks gestaion) till 24 weeks gestation. Randomization will be performed through the use of a computer-generated list of random numbers in blocks of 6 by a study coordinator. Treatment assignments will be concealed in consecutively-numbered sealed envelopes, which will be opened sequentially upon subject enrollment. The interventionists (the dietitian and the exercise instructor), the subjects and the study coordinator will not be blinded to the treatment assignment. However, the interventionists will not take outcome measurements. Subjects will be reminded not to reveal information about their intervention to the outcome assessors, clinicians and nurses of routine antenatal and postnatal care. All investigators, outcome assessors, clinicians and nurses of routine antenatal and postnatal care will be blinded to the treatment assignment.  Data will be collected by trained research staff at six time points, namely <=12 weeks gestation (baseline/T0), 16-20 weeks gestation (T1), 24-28 weeks gestation (T2), 35-37 weeks gestation (T3), within 48 hours of delivery (T4), and 6-8 weeks postpartum (T5). These time points are scheduled mostly together with the routine AN care visits to minimize subjects’ burden for extra visits for the study. A cash of HK$50 per visit will be payable to each subject at T1, T2, T3 and T5.  **Intervention group** – In addition to receive routine antenatal care, subjects randomized to the intervention group will participate in a dietitian-led LMP from the first AN booking (i.e. <=12 weeks gestation) to 24 weeks gestation. The original LMP is based on a strategy of increasing energy expenditure and reducing caloric intake using lifestyle behavioral change to achieve long-lasting impact. It generally requires participants to attend dietary consultation sessions weekly in the first 3-4 months, and monthly in the subsequent months, and to see an exercise instructor at least once during the program. However, considering that frequent visits may be a burden for pregnant women but frequent contacts in early stage of pregnancy are important for effective lifestyle intervention (21); the original LMP will be modified in several aspects. Firstly, consultations will be scheduled bi-weekly instead of weekly in the first 2 months of the program and monthly to the end of the program (i.e. 24 weeks gestation). Secondly, some original face-to-face consultations in the first two months will be replaced by telephone consultations since the effectiveness of high-frequency (i.e. weekly) telephone contact with a dietitian was comparable to high-frequency face-to-face lifestyle counseling in supporting obese patients trying to lose weight (21). Thirdly, the consultation sessions will be mostly scheduled on the same day of the routine AN visits of the subjects.  At the first session (about 1 hour), the dietitian will carry out a complete behavioral assessment, covering important areas such as the subject’s pre-pregnant and current weight status, eating and lifestyle patterns, specific eating-related behaviors, traditional food taboos in pregnancy, knowledge of risks associated with current eating patterns, and concerns and feelings about specific lifestyle changes. The dietitian will review the subject’s medical, pregnant and birth history, and the weight gain in previous pregnancy. Moreover, the dietitian will review the fetal growth and the subject’s weight gain of current pregnancy, and discuss the specific dietary and lifestyle advices to achieve a desirable weight status with the subjects.  In the follow-up consultation sessions (about 20 minutes), the dietitian will review the subject’s dietary and lifestyle practices and provide recommendations. Each subject will be given an individualized menu plan aiming at achieving a varied balanced diet and a desirable fetal growth and maternal weight throughout pregnancy. The dietary component of the menu plan will be based on the American Dietetic Association’s recommendations (22). A varied balanced diet with an emphasis on fruit and vegetables, and moderate-carbohydrate, low-fat, low-GI and low-calorific products in appropriate portions will be encouraged. Each subject will be provided with two booklets, one for food portion size exchange and tips for eating out, and another listing the low-GI food options and meal plans (GI <55). Moreover, advice on use of dietary supplements and managing food cravings, nausea, vomiting and constipation will be given. Techniques for coping at-risk situations such as parties and festival celebrations will be taught. Recipes will be provided to the subjects to encourage healthy cooking. The dietitian will also encourage the subjects to send their enquiries to the dietitian by emails.  Besides, subjects will be encouraged to see an exercise instructor at least once during the LMP, which will be tried to schedule on the same day as the dietitian appointment and/or AN visits for subjects’ convenience. The exercise instructor will arrange individualized follow-up session based on his/her clinical judgment. Subjects will be encouraged to request for exercise consultations as often as they feel necessary. Ongoing support from the exercise instructor will also be available by phone calls or emails. During the exercise consultation (about 30 minutes), the exercise instructor will review subject’s medical history as well as pre-pregnant and current exercise habits, and assess subject’s fitness level and musculoskeletal problems. The exercise instructor will design a suitable exercise regime for the subject. Medical clearance is recommended for women who have been sedentary before pregnancy or who have a medical condition. The exercise instructor will use the PARmed-X for Pregnancy as a guideline for health screening for the subjects prior to participation in a prenatal fitness class or other exercise, and use the information as a reference to decide the individualized exercise prescription and the program safety. During the first trimester, pregnant women who were previously exercising may continue but modify the exercise regime in accordance with general physiological changes, like high to low impact exercise, while inactive women should refrain from exercise until the second trimester. After the first trimester, subjects will generally be advised to do a 30-minute of easy to moderate intensity of low impact aerobic exercise, including brisk walking, stationary bike, swimming or walking in water for at least three times a week. Subjects will be asked to work out at a manageable intensity which talking could be done without difficulty and with slightly elevated heart rate and breathing rate. For easy indication, the exercise instructor will ask the subjects to weigh their rate of exertion by using the 10-point Borg scale and level 1-4 indicates the exercise intensity as easy to somewhat hard. The exercise instructor will demonstrate techniques for static stretching (avoiding muscle pain) of most muscle groups (upper and lower limbs, neck and trunk muscles) to the subjects. Moreover, the exercise instructor will show to the subjects how to do resistance training, covering the major muscle groups of the arms, abdomen and legs to promote good posture, prevent low back pain and lower limb join problems. Subjects will receive written exercise prescription with frequency and duration targets, and brochures including examples for adequate exercise. Information regarding precautions of participation in a prenatal fitness class or other exercise, such as supine position over 16 weeks, overheating, breath holding and long standing will be provided to the subjects. Information regarding warning signs, such as excessive shortness of breath, dizziness and fainting to terminate exercise and when medical advice should be sought will also be provided.  To check the adherence to both diet and exercise intervention, 3-day dietary records, daily activity log sheets, pedometer readings and attendance data will be used. Participants’ adherence to both the diet and exercise intervention will be assessed by a check-list and an adherence score to each of the diet component and the exercise component will be generated. 1 score will be given for meeting each of the key recommendations given by the dietitian or the exercise instructor. Higher score indicates the participant being more adherent to the LMP.  For the diet adherence score, 1 score will be given for meeting each of the criteria below: (i) total energy not exceeding 10% of the diet plan; (ii) % energy from fat 20-30%; (iii) % energy from protein within the range of 15-20%; (iv) % energy from carbohydrate 50-60%; (v) consumption of fruit > 160g; (vi) consumption of vegetables > 240g (equivalent to 1-2 servings of fruits and 3-4 servings of vegetables); (vii) regular meal consumption as prescribed by dietitian and (viii) “Avoid food (e.g. high fat or high sugar foods/glycaemic index foods)” not being consumed. The scores will be summed up to give a dietary adherence score, ranging from 0 to 8 and a maximum of 24 scores (8 scores x 3 day) for each follow-up time point. Adherence to dietary intervention will also be assessed by calculating the percentage attendance to the intervention sessions.  Regarding the physical activity adherence, the score will be assessed based on the IPAQ-C data. Two scores will be given if 80% of the recommended volume of exercise (frequency x duration) was met during the week of follow up (7 days) while one score will be given if 50% of the recommended volume of exercise was achieved. Zero score will be given for those who did not perform any easy to moderate intensity of low impact aerobic exercise. Number of exercise consultation sessions attended by the subjects will also be documented.  To measure physical activity level more objectively, we will also use pedometers as an objective measurement to tally steps taken by the participants. However, due to limited funding budget, only a sub-group (25%) of subjects in each arm, who will be randomly chosen and will be given a pedometer to record daily step counts for up to seven consecutive days at various time points. The pedometer readings will be filled daily for 7 days at each time point.  **Control group** - Subjects in the control group will receive routine antenatal care shared between the Li Ka Shing outpatient clinic of the PWH and the Maternal and Child Health centres. The subjects will be provided with an educational pamphlet on diet and exercise during pregnancy and offered optional antenatal classes which subjected to quotas availability. An updated protocol has been implemented in the PWH since 1st May 2014 to standardize the screening, diagnosis and management of GDM.  **Measurements –** Various maternal and fetal/neonatal data will be collected using standardized methods and questionnaires, and retrieved from the hospital record.   - **Maternal physical examination measurements:** Weight, height, blood pressure and heart rate will be measured using standardized methods, and pre-pregnancy weight will be self-reported. The total gestational weight gain will be calculated as the difference in the weight measured on the day of delivery and self-reported pre-pregnancy weight. - **Maternal Laboratory assessments:** A 75 g 2-h OGTT will be done at 24-28 weeks gestation on routine AN care basis. GDM will be diagnosed using the modified WHO criteria. In the study hospital, a new protocol of diagnosis of GDM has been implemented since 1st May 2014. Only the fasting plasma glucose (FPG) and 2-h plasma glucose (PG) results of the OGTT instead of the fasting, 1-h and 2-h PG results will be used as diagnostic criteria for GDM due to resource constraints. Therefore, the primary outcome (i.e. GDM) will be diagnosed between 24-28 weeks of gestation if one or more of the following criteria are met: (i) FPG 5.1-6.9 mmol/L; (ii) 2-hour PG 8.5-11.0 mmol/L following a 75g oral glucose load. Extra OGTT will be repeated at 6-8 weeks postpartum for those who have abnormal OGTT results at 24-28 weeks gestation. - **Demographic and other lifestyle habits**, such as mother’s age, occupation, family income, smoking status and alcohol use will be collected using a standardized questionnaire at baseline. Smoking status and alcohol use will be asked again at 35-37 week gestation to check for any changes in these habits during pregnancy. - **Medical history, past/current obstetric history, medication use** will be retrieved from the hospital record and collected using a questionnaire at baseline and at 35-37 weeks gestation. - **Dietary intakes, physical activity level and use of supplements** will be assessed. A 3-day diet record including one weekend day and two weekdays will be used to assess subject’s diet. Daily nutrient intake and consumption of food group of all subjects at various time points will be calculated using the nutrition analysis software Food Processor Nutrition analysis and Fitness software version 8.0 (ESHA Research, Salem, USA) including local foods selected from food composition tables from China and Hong Kong. Since there has been no validated Chinese questionnaire for measuring physical activity level for pregnant women, the present study will use a Chinese version of the International Physical Activity Questionnaire (IPAQ-C) which has been validated among general Chinese population (23). Moreover, a general physical activity questionnaire capturing special physical activity patterns of pregnant women will be asked. A sub-group (25%, n=28) of subjects in each arm, who will be randomly chosen and be be given a pedometer (Yamax brand) to record daily step counts for up to seven consecutive days at various time points. The pedometer readings will be filled daily for 7 days at each time point. Data on use of supplements will be collected by asking subjects to specify the brand, the frequency, and the dosage of supplements used. - **Perceived support from the dietitian and the exercise instructor** will be assessed at 24-28 weeks of gestation (T2) using the Health Care Climate Questionnaire (HCCQ), a 15-item patient-rated measures on a scale of 1 (strongly disagree) to 7 (strongly agree) related to their perceived supportiveness of health care providers. HCCQ is validated among various settings. The Chinese version was validated with high internal reliability (0.93) (24). - **Perinatal and obstetric outcomes, neonatal outcomes and complications** will be retrieved from the hospital record. Perinatal and obstetric outcomes and complications will include GDM as measured by OGTT at 24-28 weeks gestation, preeclampsia, gestational hypertension, Caesarean section and preterm delivery, and gestation at delivery (week). Fetal and neonatal outcomes will include fetal ultrasound, Apgar score at 1 minute and 5 minutes, neonatal weight and length, head circumference, LGA, macrosomia and shoulder dystocia. |
|  |
| **Data processing and analysis**  Data will be presented as mean (standard deviation), median (inter-quartile range) for skewed variables and frequency (percentage) as appropriate. Skewed variables will be corrected by necessary transformations before statistical analyses. Between-groups comparisons at baseline and after intervention will be made using the Student’s t test, Chi-square test or Fisher’s exact test, as appropriate. Multilevel models will be used to compare differences between the 2 groups for all measured outcomes including GDM prevalence, proportion of infants born LGA and macrosomia, anthropometric measures and other obstetric maternal outcomes and fetal and neonatal outcomes at baseline and 24-28 weeks gestation or at delivery with adjustment for age and other covariates. Multilevel model can be used to analyse both longitudinal continuous and discrete data (25). All statistical tests are two-sided and a p-value <0.05 is considered statistically significant. SPSS for Windows software (version 24.0, SPSS Inc., Chicago, IL, USA) will be used for the statistics. |

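### A single printed block size of 6, run by an unblinded coordinator with list-making and enrolment not separated, leaves up to a quarter of assignments foreseeable to anyone who sees earlier ones

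*Protocol*

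**What the plan says.** All of this is in section 3 of the protocol (Plan of Investigation).

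- **Sequence.** "Randomization will be performed through the use of a computer-generated list of random numbers in blocks of 6 by a study coordinator". Allocation is 1:1, and no stratification is mentioned.
- **Concealment.** "Treatment assignments will be concealed in consecutively-numbered sealed envelopes, which will be opened sequentially upon subject enrollment". The protocol does not say who prepares the envelopes, who opens them, or who learns the result.
- **Unblinded roles.** The dietitian, the exercise instructor, and "the subjects and the study coordinator will not be blinded to the treatment assignment".
- **Blinded roles.** "All investigators, outcome assessors, clinicians and nurses of routine antenatal and postnatal care will be blinded to the treatment assignment".
- **Design label.** "This will be a parallel group, single-blind randomized controlled trial".
- **Recruitment.** Women are recruited by convenience sampling at the first booking visit of one hospital. Research staff screen, check eligibility, explain the study and invite. As recruiters, these staff appear on neither the blinded nor the unblinded list.
- **Size.** 110 women per group are to be randomised, 220 in all.

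**The concern.** A sealed envelope hides the next assignment only if it cannot be worked out from those already opened. With one list, one hospital and one known block length, a person who has seen the earlier assignments in a block can often infer the rest. The last place in every block is always determined.

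Recruitment leaves room to act on that knowledge. Sampling is by convenience, and any one of several risk criteria qualifies a woman, so eligible women may differ considerably in their risk of gestational diabetes. Willingness to follow study procedures is also partly a judgement. If better-motivated or lower-risk women were invited when the intervention was due, the comparison would tilt towards the programme. The planned adjustment for age and other covariates would not fully remove selection on unmeasured motivation. Blinded assessors and a laboratory glucose test do not help here, because they protect measurement and the problem would arise at entry.

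**Working it through.** **Inputs from the protocol:** block size 6; ratio 1:1, hence 3 + 3 per block; 220 women. The protocol gives no predictability figure to reproduce.

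**Assumed observer (upper bound):** knows the block size, where blocks start, and every earlier assignment in the block.

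**1. Assignments known with certainty.** A block has C(6,3) = 20 equally likely orders. A place is determined once one arm has used its 3 slots.

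- Places 1 to 3: never.
- Place 4: the first three are all in one arm, 2/20 = 10%.
- Place 5: the last two are in the same arm, 2 × C(4,1)/20 = 8/20 = 40%.
- Place 6: always, 100%.

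Expected per block: 0.1 + 0.4 + 1.0 = 1.5 of 6 = 25.0%. The closed form 2b/(b+1) with b = 3 gives 6/4 = 1.5, in agreement.

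Over 220 women there are 36 full blocks (216) plus 4 places: 36 × 1.5 + 0.1 = 54.1, or 54.1/220 = 24.6%.

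**2. Correct guesses.** The observer always bets on the arm with more slots left.

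| Place | Chance of a correct guess |
|---|---|
| 1 | 0.5 |
| 2 | 3/5 = 0.6 |
| 3 | 0.4 × 0.75 + 0.6 × 0.5 = 0.6 |
| 4 | 0.1 × 1 + 0.9 × 2/3 = 0.7 |
| 5 | 0.4 × 1 + 0.6 × 0.5 = 0.7 |
| 6 | 1.0 |

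The sum is 4.1, and 4.1/6 = 68.3%, against 50% by chance.

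**3. Lower bound.** A recruiter who does not know earlier assignments has nothing to infer from: 0% certain.

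**4. Effect of varying the block size.** Simulation of 220 assignments, 1,000 runs. The observer knows the set of possible sizes and all earlier assignments, but not the size of the current block.

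| Block sizes | Certain | Best guess correct |
|---|---|---|
| 6 only | 24.6% | 68.2% |
| 4, 6 | 5.5% | 69.3% |
| 4, 6, 8 | 2.4% | 68.0% |

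Varying sizes removes most of the certainty and almost none of the guessability. Only withholding earlier assignments removes both.

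**5. What selection could do (illustration on assumed figures).** Suppose every determined slot were exploited, and the women steered into those slots had a risk of gestational diabetes 5 to 10 percentage points lower than average in the intervention arm and as much higher in the control arm. The difference between arms would shift by 2 × 0.25 × 5 = 2.5 to 2 × 0.25 × 10 = 5 points. The protocol offers no evidence that this would happen. The figure only shows the scale of the worst case, against a planning difference of 29% − 6% = 23 points.

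**The case against.** The case on the other side has real force.

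- **The trial is not open-label.** A reader might infer that it is, since subjects know their arm. The protocol calls it single-blind and blinds investigators, outcome assessors and routine-care staff. Only subjects, the two interventionists and the coordinator are unblinded. This stands.
- **A quarter of assignments are not shown to be predictable in practice.** A reader might take 25% as a property of the trial. It needs a recruiter who has seen every earlier assignment, and the protocol nowhere says recruiters do. Research staff also collect the data at all six time points, and outcome assessors are blinded. If recruiters and assessors are the same people, they may already be shielded. This stands, and it is why the result is a range. Equally, the protocol does not say they are the same people or that recruiters are shielded.
- **The coordinator is a separate matter.** Whoever holds the list knows all of it whatever the block size, so 25% and 68% do not describe that risk. Nor does the protocol say the coordinator recruits; it gives screening and invitation to research staff. This stands. What remains is that nothing keeps list preparation apart from enrolment and envelope opening.
- **Concealment is already specified.** Numbered sealed envelopes are opened in order at enrolment, and written consent is required. These hide the next assignment directly, but they do not prevent inference from those already opened.
- **Permuted blocks are standard, and the rest is silence.** Permuted blocks contradict nothing in the document. But the single block length is not an omission: the protocol chooses it and prints it, next to an unblinded person who runs the randomisation.

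**Conclusion.** The point holds in a limited form. The protocol fixes and discloses one block size at one hospital, has an unblinded coordinator perform the randomisation, and does not separate that task from enrolment or envelope opening. This leaves avoidable predictability of between 0% and 25% certain assignments (0 to about 54 of 220), with a best-guess rate of up to 68%. The upper end assumes full knowledge of the block size and of earlier assignments. The lower end assumes recruiters see no earlier assignments. The document does not settle which applies.

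It does not show that selection would occur, and it casts no doubt on how the primary outcome is measured. The matter is worth correcting because the change is nearly free and because selection at entry cannot be fully repaired in the analysis.

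**What to change.** Change the Trial procedures text in four respects:

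1. Use randomly varying block sizes, for example 4, 6 and 8 in random order, and keep the sizes out of any document available to recruiting staff.
2. Have the list and envelopes prepared by an existing team member who takes no part in screening, consent or envelope opening, and say so.
3. State that staff who screen and invite are not shown earlier assignments. This matters most, since step 1 alone leaves the guess rate near 68%.
4. State who opens each envelope, and that it is opened only after consent and baseline data are recorded.

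**Cost:** a new computer list, a reallocation of tasks and a few sentences, with no extra staff or visits. The changes need to be in place before enrolment. **Downside:** a slightly larger possible imbalance wherever recruitment stops. The largest within-block difference rises from 3 women (half of 6) to 4 (half of 8), which is negligible with 110 per group.

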**Principal Investigator: [name] [name]**

**Research Assistant Professor**

**Department of Medicine and Therapeutics**

**The Chinese University of Hong Kong**

**1. BACKGROUND**

**Global burden of gestation diabetes mellitus (GDM)**

Gestational diabetes mellitus (GDM) is defined as a type of diabetes first diagnosed during pregnancy (1). With the increasing prevalence of obesity and diabetes worldwide, in particular type 2 diabetes among women, there have been increasing number of women with GDM (2). GDM affects 1% to 14% of pregnancies, depending on the population studied and the diagnostic tests used (3). Maternal glucose level has been associated with a range of adverse maternal and pregnancy outcomes. Women with GDM have an increased risk for developing the metabolic syndrome and early markers of vascular diseases such as disturbed endothelial function (4). GDM has also been linked with higher rates of cesarean sections, induced deliveries, shoulder dystocia and macrosomia, and pathogenesis in the offspring of overweight and metabolic syndrome (4).

Accumulating evidence suggests that an adverse environment during in utero orpostnatal periods are related to the development of obesity and associated disorders later in life. Overseas findings of human studies accumulate that intrauterine or postnatal nutrition has a major impact not only on immediate outcomes, such as growth, but also on long-term health later in life (5). Therefore, the importance of timely intervention at early life in reducing the lifetime burden from non-communicable diseases (NCDs) has been promoted (6).

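### The primary GDM definition is closed at the top, so read literally a woman whose glucose lies above a band, with neither value inside one, is not an event

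*Protocol*

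**What the plan says.** All of the following is in the Protocol.

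- Section 3, Study outcomes, sets a binary endpoint: "The primary outcome will be the proportion of subjects developed GDM at 24-28 weeks gestation".
- Section 3, Measurements (Maternal Laboratory assessments), makes it operational. The outcome "will be diagnosed between 24-28 weeks of gestation if one or more of the following criteria are met", and the criteria are "i) FPG 5.1-6.9 mmol/L; (ii) 2-hour PG 8.5-11.0 mmol/L following a 75g oral glucose load".
- Section 1, Background, describes the condition more widely: "Gestational diabetes mellitus (GDM) is defined as a type of diabetes first diagnosed during pregnancy". That wording has no upper glucose limit.
- The exclusion criteria in section 3 list "Pre-existing DM". No glucose test at baseline is described.
- The one instruction about abnormal results concerns follow-up: "Extra OGTT will be repeated at 6-8 weeks postpartum for those who have abnormal OGTT results at 24-28 weeks gestation".
- Section 4, Subject withdrawal, allows women later found to have breached an entry criterion to stay in the study unless the investigator judges otherwise.

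**The concern.** An endpoint meant to record raised glucose should not stop recording it when glucose is higher still. With both bands closed at the top, some women with the highest values fall outside the rule, while a woman with FPG 5.3 and 2-h PG 7.5 is inside it.

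Nothing else in the document brings them back. The diabetes exclusion acts at entry and has no described glucose test behind it, so it does not deal with values first seen at 24-28 weeks. The postpartum retest does not score the outcome. The withdrawal section says who may remain, not how she is counted. Recruitment is limited to women at high risk of GDM, so values above the bands are possible.

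At stake is a small number of primary events, whose handling would otherwise be settled after the values are known.

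**Working it through.** **1. The rule applied to example pairs.** As written, the event is (5.1 ≤ FPG ≤ 6.9) or (8.5 ≤ 2-h PG ≤ 11.0). The comparison rule keeps the lower limits and drops the upper ones.

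| FPG / 2-h PG (mmol/L) | As written | No upper limit |
|---|---|---|
| 4.8 / 7.5 | no | no |
| 5.3 / 7.5 | event | event |
| 7.2 / 9.0 | event | event |
| 6.0 / 12.0 | event | event |
| 7.2 / 7.5 | no | event |
| 4.8 / 11.5 | no | event |
| 7.5 / 12.5 | no | event |

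The rules differ only for women with at least one value above its band and neither value inside a band. A high value alone does not remove a woman: 7.2/9.0 and 6.0/12.0 still count.

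**2. The plan's own sample size.** The inputs, from Sample size calculation, are "6% subjects developed GDM in the intervention group compared to 29% in control group" and "two-sided test will be 42 per group with power of 80% at a 5% significance level".

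Pooled formula: n = [z(1−α/2)·√(2p̄(1−p̄)) + z(power)·√(pC(1−pC) + pI(1−pI))]² / (pC − pI)², with pC = 0.29, pI = 0.06 and p̄ = 0.175.

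- 5% alpha, 80% power: 41.6, so 42 per group, as stated.
- 1% alpha, 90% power: 78.7, so 79 by this formula. The unpooled formula gives 73.8 and the arcsine formula 72.1 (73 rounded up), so the stated 73 is in line with those.
- Attrition: 73 / (0.70 × 0.95) = 109.8, so 110, as stated.

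The point about the definition does not depend on these figures.

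**3. Illustrative effect on power.** The document does not say how many women would fall outside the bands, so a range is assumed: 5%, 10% or 15% of control events lost and none in the intervention arm. The control-only placement is the unfavourable case for power. Exact power is the sum, over all pairs (x, y), of Bin(x; 73, pC) × Bin(y; 73, pI) where the two-sided uncorrected chi-square test rejects. Both 1% (the sample-size level) and 5% (the level in Data processing and analysis) are shown, with pI = 6%.

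| Control events lost | Women lost (73 × 0.29 × share) | Control rate counted | Power, 1% | Power, 5% |
|---|---|---|---|---|
| 0% | 0 | 29.0% | 90% | 97% |
| 5% | 1.1 | 27.6% | 86% | 96% |
| 10% | 2.1 | 26.1% | 81% | 94% |
| 15% | 3.2 | 24.7% | 75% | 91% |

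**4. Direction.** Take an assumed 3 percentage points of women uncounted.

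- Control arm only: 26% − 6% = 20 points.
- Intervention arm only: 29% − 3% = 26 points.
- Both arms equally: 26% − 3% = 23 points, the same as planned.

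The sign of any distortion depends on which arm holds the excess.

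**The case against.** The best reply is that the protocol says when GDM is diagnosed but never says that a woman above the bands counts as free of it, or that she stays in the denominator. She might be treated as an event, as a separate category, or as a late-found breach of the diabetes exclusion. An analysis plan not shown here could settle this. The upper limits may also serve to separate GDM from other diabetes.

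Part of this stands. Scoring her as a success is what the literal rule produces for a binary outcome over all subjects; it is not a stated intention. But the protocol does not leave the definition open. It fixes it with numbers, and an analysis plan that applied them faithfully would inherit the gap. A purpose for clinical labels does not settle how the trial counts her.

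Three stronger readings are tempting and are not supported:

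- **Any woman above a limit becomes a success.** She does not if her other value is inside its band, because one criterion is enough.
- **The comparison is biased towards no effect.** That needs more uncounted women in the control arm. The document gives no counts, and step 4 shows that the opposite is possible.
- **The significance of the result hangs on it.** With 73 per arm and an uncorrected chi-square, 21 vs 10 events gives p = 0.026 and 19 vs 10 gives p = 0.062. But 10 of 73 is not a planned rate; the pair was chosen near the threshold. At about the planned counts, 21 vs 4 gives p = 0.0002 and 19 vs 4 gives p = 0.0007.

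**Conclusion.** The point holds in a limited form. The operational definition in section 3 leaves out women with at least one value above its band and neither inside one, and it does not fit the wider description of GDM in section 1. The number affected is unknown and probably small.

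On the unfavourable assumption that 5-15% of control events and no intervention events are lost, power falls from 90% to between 86% and 75% at 1% alpha, and from 97% to between 96% and 91% at 5%. These figures rest on the planned 29% vs 6%, on 73 evaluable women per arm, and on a share lost that the document does not supply. The defect merits correction because it sits in the primary endpoint and is cheap to remove, but it does not put the trial's conclusion in doubt by itself.

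**What to change.** For the trial endpoint only, state that a woman is an event if FPG is at least 5.1 mmol/L or 2-h PG is at least 8.5 mmol/L at the 24-28 week OGTT, with no upper limit. Report women above 6.9 or 11.0 mmol/L as a separate row by arm, and repeat the primary comparison with the banded definition as a sensitivity analysis. Reconcile the description in section 1 with the criteria in section 3. Clinical diagnostic labels and management are not touched.

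The cost is about a sentence in the outcome definition, one table row and one repeat analysis. The OGTT values are already collected and the sample size does not change. The downside is that the endpoint becomes GDM or higher glucose, and may take in some unrecognised pre-existing diabetes. Randomisation should balance that between arms, and the separate row would show how much there is.
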